### Statistical analysis

#### Sample size

In this study, a cluster randomized design is used. The primary endpoint of the study is death rate, which will be determined by survival analysis. According to the IDEAL study, the death rate was 37% during a median follow-up period of 3.59 years [9]. Because we include relatively stable patients the mortality rate may be lower; we assume the death rate will be 30% or less within 3 years. The project selection window for patient enrollment is 30 months. Sood et al. found an adjusted facility-level intraclass correlation coefficient (ICC) of 0.031 in their work [16]. We get 8 clusters per group. Scholars have proposed that a sample size calculated assuming individual randomization can be inflated by a Design Effect (DE) to reach the required level of statistical power under cluster randomization [17]: DE = 1+ (m-1) ρ, where m is the number of individuals per cluster and ρ is the ICC.

If we assume that alpha = 5%, (1-beta) = 80%, patients are assigned 1:1, a difference of 10% in death rates between these two groups is considered acceptable. We use log-rank tests to get the events (87 vs 57) with the Power Analysis and Sample Size Software, version 13 (NCSS, LLC. Kaysville, Utah, USA) and the number of individuals per group is 473. Thus, the number of total events under the consideration of cluster effects is 198 (128 vs 70). This is an endpoint driven study. We will complete the study when we get enough endpoint events, which is 198 events.

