**Methods:**

The trial adopts a multicenter, cluster randomized, single-blind (outcomes assessor), and endpoint-driven design. Eligible participants are 18–80 years old, in stable CKD stages 4–5 (eGFR > 7 ml/min /1.73 m^2^), and with good heart function (NYHA grade I or II). Participants will be randomized into a routine or deferred dialysis group. The reference eGFR at initiating dialysis for asymptomatic patients is 7 ml/min /1.73 m^2^ (routine dialysis group) and 5 ml/min/1.73 m^2^ or less (deferred dialysis group) in each group. The primary endpoint will be the difference of all-cause mortality and acute nonfatal cerebro-cardiovascular events between the two groups. The secondary outcomes include hospitalization rate and other safety indices. The primary and secondary outcomes will be analyzed by appropriate statistical methods.

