### Endpoints

#### Primary endpoint

The primary endpoint will be all-cause mortality and acute nonfatal cerebro-cardiovascular events before and after dialysis initiation. We will compare proportions of all-cause death rates and acute nonfatal cerebro-cardiovascular events before and after dialysis treatment between two groups.

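### The primary endpoint is stated in two ways, so the event whose 198th occurrence closes the trial is undetermined

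*Protocol article*

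**What the plan says.** The Abstract (Methods) states: "The primary endpoint will be the difference of all-cause mortality and acute nonfatal cerebro-cardiovascular events between the two groups". The Primary endpoint section agrees: "The primary endpoint will be all-cause mortality and acute nonfatal cerebro-cardiovascular events before and after dialysis initiation".

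The Sample size section names something else: "The primary endpoint of the study is death rate, which will be determined by survival analysis". Its inputs are all death rates. It cites 37% from the earlier randomized trial, then says "we assume the death rate will be 30% or less within 3 years", and sets the effect as "a difference of 10% in death rates between these two groups is considered acceptable". With "alpha = 5%, (1-beta) = 80%, patients are assigned 1:1", a log-rank calculation gives 144 events (87 and 57), which is raised to 198 (128 and 70) for clustering. The section ends: "We will complete the study when we get enough endpoint events, which is 198 events".

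The Analysis section lists mortality and nonfatal events as items for Cox analysis beside hospitalization. It names no combined first-event variable.

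**The concern.** In an event-driven trial, the definition of a countable event fixes when the trial ends, what the primary test compares and what the power statement refers to. Here two sections give one definition, a third gives another, and the closing rule uses a generic term that fits both.

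The Discussion says that counting events protects power if event rates turn out lower than predicted. That holds only if the event being counted is the event that was powered. The rule also acts while the trial is running, so a later analysis plan cannot undo a closure triggered by the wrong count.

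**Working it through.** **Step 1: which event was the target built on?** Inputs from the Sample size section: 30% deaths at 3 years, a 10-point difference, alpha 5%, power 80%, 1:1 allocation. The article does not give the direction of the difference or the sidedness. I read them as 30% against 20%, two-sided.

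- Hazard ratio = ln(0.80)/ln(0.70) = 0.626, so |ln HR| = 0.469.
- Schoenfeld: 4 × (1.960 + 0.842)² / 0.469² = 143 events.
- Freedman: (1.626/0.374)² × (1.960 + 0.842)² = 148 events.
- Stated: 87 + 57 = 144, within 3% of both.
- Split by group: 87/0.30 = 290 and 57/0.20 = 285 patients, which is consistent with near-equal groups at 30% and 20% deaths.
- Alternatives do not fit: one-sided testing gives 113 or 117 events, and 30% against 40% gives 244 or 249.

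The 144 is therefore a number of deaths. No rate or effect for nonfatal events, or for a combined endpoint, appears anywhere in the article.

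**Step 2: the inflation actually used.** 198/144 = 1.375. I take this as given. Whether it follows from the stated ICC and cluster size is a separate question and is not used here.

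**Step 3: are 198 deaths reachable?** With 473 per group at 30% and 20%, deaths by 3 years are 141.9 + 94.6 = about 237. Counting deaths alone is therefore a workable reading.

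**Step 4: what if nonfatal events also count?** The mix of events is not in the article, so the first column is an assumption. It gives patients counted only for a nonfatal event (alive at closure) as a percentage of deaths. Deaths at closure are D = 198/(1 + that fraction). Power for death = Φ(0.469 × √(D/1.375/4) − 1.96).

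| Nonfatal-only patients, relative to deaths (assumed) | Deaths D | D/1.375 | Power for death |
|---|---|---|---|
| 0% | 198 | 144 | 80% |
| 30% | 152 | 111 | 69% |
| 50% | 132 | 96 | 63% |
| 100% | 99 | 72 | 51% |

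Deaths drop below even the unclustered 144 once their share of the counted events is under 144/198 = 73%, that is, once nonfatal-only patients add more than 37.5%.

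These powers are for the log-rank comparison in the Sample size section.

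**The case against.** The strongest reply is that the Sample size section is consistent within itself. Every input is a death rate and 128 against 70 follows from them, so 198 most naturally means deaths, and on that reading no deaths are lost. This is fair, but it leaves the Abstract and the Primary endpoint section contradicted, and the term in the closing rule is still open to their definition.

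A second reply is that the table measures death on the one reading where death alone is not primary. If a combined endpoint had the same hazard ratio, 198 combined events would give the same power as 198 deaths. This stands. The table shows what would happen to the comparison the trial was sized on; it does not show that a combined endpoint is underpowered. Power for that endpoint is simply unsupported.

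Four stronger readings are tempting and do not hold:

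- *The trial will close far short of its planned deaths.* That depends on an event mix the article does not give. At an added 30%, deaths (152) still exceed 144.
- *Power starts at 50% and falls to 29%.* Those figures come from applying a design effect of 2.80 (473/8 = 59.1 per cluster, ICC 0.031) to a target the article presents as already inflated. The fall from 80% to 50% is a separate design-effect matter.
- *There are four primary tests, with a family-wise error of 18.5%* (1 − 0.95⁴, if independent). This reads death and nonfatal events, each before and after dialysis, as separate tests. The wording may only mean that all follow-up counts, and no section says that any one success suffices. Multiplicity is also commonly left to the analysis plan.
- *The combined endpoint must prevail.* The article never uses the word composite, and its text also fits two separate outcomes. Nothing in it settles which endpoint should be kept.

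**Conclusion.** The concern holds as an explicit contradiction within the article. It cannot be put down to condensation, because the article states two different primary endpoints and ties its closing rule to neither. The event that ends the trial is undetermined.

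The certain consequence is qualitative: one reading leaves the 80% power without a rate or effect behind it, and the other leaves the declared primary endpoint unsized. The fall in power for death from 80% to between 69% and 51% is an illustration. It rests on the assumed event mix, a hazard ratio of 0.626 (30% against 20%, two-sided) and the article's implied inflation of 1.375. It should not be read as a forecast. Because the rule controls closure, it needs settling before the count is used to end the trial.

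**What to change.** State one and the same primary endpoint in the Abstract, Primary endpoint, Sample size and Analysis sections. Either option is coherent, and the choice is the sponsor's:

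1. **Combined endpoint.** Time from inclusion to the first of death from any cause or an acute nonfatal cerebro-cardiovascular event, with one event per patient. Replace the death-only inputs in the Sample size section with assumed combined rates and an assumed effect, and restate the event target and power.
2. **Death from any cause.** Count only deaths toward the target and make the nonfatal events secondary.

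In both cases, reword the closing rule so that it names the events that count toward the closing number. The choice should be made without sight of results by group.

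The cost is modest. The Follow-up section already has nonfatal events reported prospectively, and the Blinding section already provides blinded assessors for the primary outcome. Option 1 needs rates that the article does not contain, plus one recalculation. The hospitals are already randomized, so a less favourable event target or power would have to be met by more follow-up or patients, or openly accepted. Option 2 keeps the present death-based inputs but narrows the declared primary endpoint.

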Recently, the Canadian Kidney Knowledge Translation and Generation Network published its study protocol “Knowledge Translation Interventions to Improve the Timing of Dialysis Initiation: Protocol for a Cluster Randomized Trial,” which aimed to evaluate the efficacy and safety of a knowledge translation intervention to promote the intent-to-defer approach in clinical practice [20]. The study designs have some similar components. However, they are very different. The emphasis of the Canadian research is to determine whether active knowledge translation intervention can reduce early dialysis starts. However, our study aims at evaluating the efficacy and safety of early and late dialysis initiation and the influence of timing on subsequent clinical outcomes directly.

An endpoint event-based power estimation is adopted in this study. It will allow all sites to finish together and avoid trial power being affected by alterations in accrual times. It will also protect the study power from lower than predicted event rates.

We acknowledge the following study limitations: (1) The results of the randomized study have limited generalizability due to the healthier nature of patients who participate in trials; (2) There may be a tendency for patients enrolled in clinical trials to alter their behavior due to awareness of being observed [19]. Thus, all patients may have relatively better outcomes; (3) Although this is facility-level research aimed at avoiding experimental contamination, the facilities in the routine group may also adopt the strategies in the delayed group unintentionally; (4) Patients in the routine group may actively delay their dialysis due to poor financial conditions. Thus, the eGFR rates may be similar at the end of the study and may endanger the power of this study; and (5) Patients with financial problems (e.g. without medical insurance) in both groups may get suboptimal medical care, which may impact their outcomes.

Even if the eGFR values of patients in both groups at dialysis initiation are low and not sufficiently different, this study will still potentially have economic, health, and scientific implications. Completing this study will add new knowledge about the timing of dialysis initiation.

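### The 198-event target does not follow from the protocol's own design effect, and at its stated ICC it falls short of 80% power for a 10-point difference

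*Protocol article*

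**What the plan says.** All of this is in the protocol article, Statistical analysis, Sample size. The error rates and allocation are "If we assume that alpha = 5%, (1-beta) = 80%, patients are assigned 1:1". The effect is given as "a difference of 10% in death rates between these two groups is considered acceptable", and the death rate is assumed to be at most 30% within 3 years. Enrolment lasts 30 months. The facility-level ICC is 0.031, and "We get 8 clusters per group". The design effect is DE = 1 + (m − 1)ρ, with m the number of patients per cluster; the section says it inflates a sample size calculated for individual randomisation.

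The results come in two steps. First: "We use log-rank tests to get the events (87 vs 57"), with 473 patients per group. Then: "Thus, the number of total events under the consideration of cluster effects is 198 (128 vs 70"). The trial ends when 198 events have occurred. The section does not say how 144 events became 198, and it states no effect other than the 10% and no power other than 80%.

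**The concern.** The section prints a formula, its inputs and a result, and they disagree. A design effect multiplies the required information in both arms by one factor. Here the number of patients is unchanged, the total number of events rises by far less than the formula requires, and the two arms rise by different factors.

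The figure matters because 198 is the stopping rule. If it carries much less than 80% power for the stated difference, the trial can end without a significant result when a 10-point difference in mortality exists. A reader who trusts the stated 80% could then take that result as good evidence that deferral does no harm.

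**Working it through.** **Inputs from the Sample size section.** Alpha 5%, power 80%, 1:1 allocation, 10-point difference, 30% reference rate at 3 years, 30-month accrual, ICC 0.031, 8 clusters per group, 473 per group, 87 vs 57 events, then 128 vs 70.

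**Inputs assumed.** Two-sided testing, 20% as the second rate, exponential survival and 36 months in total. Step 1 supports them, because together they reproduce the plan's figures. One-sided testing would need only 113 events.

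**Step 1: the figures before any cluster allowance.**
- HR = ln 0.8 / ln 0.7 = 0.626, so ln HR = −0.469.
- Schoenfeld events = 4(1.96 + 0.842)²/0.469² = 143 (Freedman 148; plan 144).
- Hazards are 0.1189 and 0.0744 per year. With follow-up uniform between 0.5 and 3 years, the event probabilities are 0.1848 and 0.1208.
- 473 × 0.1848 = 87.4 and 473 × 0.1208 = 57.1 (plan 87 and 57).

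So 473 and 87 vs 57 reproduce under individual randomisation, with no cluster inflation.

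**Step 2: the plan's design effect applied.**
- m = 473/8 = 59.125, so DE = 1 + 58.125 × 0.031 = 2.80.
- 144 × 2.80 = about 403 events, against 198 in the plan.
- The factor actually used is 198/144 = 1.375, which would need an ICC of 0.375/58.125 = 0.0065.
- By arm, 128/87 = 1.47 and 70/57 = 1.23. No single design effect gives both.

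**Step 3: what 128 vs 70 corresponds to.**
- 128/473 = 27.1% and 70/473 = 14.8%, a gap of 12.3 points. HR = ln(1 − 0.148)/ln(1 − 0.271) = 0.51.
- Effective size per arm = 473/2.80 = 168.8. Unpooled SE = 0.0438, so z = 0.1226/0.0438 = 2.80.
- Power is 80.0% (unpooled normal), about 79% (pooled) or 74% (noncentral t, 14 df).

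**Step 4: power for the stated effect.**
- 198 events at HR 0.626: 198/2.80 = 70.7 effective events. z = 0.469 × √(70.7/4) = 1.97, so power is 50% (normal) or 45% (14 df).
- 10-point gaps with 473 per arm and DE 2.80:

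| Rates | Power, 14 df | Power, normal |
|---|---|---|
| 30% vs 20% | 51% | 57% |
| 25% vs 15% | 58% | 64% |
| 20% vs 10% | 68% | 74% |

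- ICC sensitivity at 198 events and HR 0.626 (normal):

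| ICC | DE | Power |
|---|---|---|
| 0.01 | 1.58 | 75% |
| 0.02 | 2.16 | 61% |
| 0.031 | 2.80 | 50% |
| 0.05 | 3.91 | 39% |

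**Step 5: the 10% read as an equivalence margin.** With two one-sided tests, no true difference, 473 per arm and DE 2.80, SE = √(2p(1 − p) × 2.80/473). Power is 2Φ(0.10/SE − 1.645) − 1, which is 28% at p = 30% and 46% at p = 20.9% (198/946).

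**The case against.** **The power figure depends on the reading.** This stands. The 45-50% belongs to HR 0.63. Among 946 patients, 198 events at that hazard ratio correspond to 25.2% vs 16.6%, a gap of 8.6 points. The protocol assumes a rate of 30% or less, and a 10-point gap lower on the scale is easier to detect. One cannot say that power for any 10-point difference is one half; it should be given as a range.

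**The ICC may not apply.** The section does not say which outcome the 0.031 describes, and an ICC near 0.0065 would make 198 events sufficient. But 0.031 is the only value the plan gives, and its target has to be consistent with it.

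**The origin of 128 vs 70 is not documented.** A reader might infer as fact that the cluster allowance was made by enlarging the effect. The match in Step 3 suggests this, but the text does not say so, and the match is exact only for one version of the test.

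**More events could restore power.** The Discussion says of the event-driven design: "It will also protect the study power from lower than predicted event rates". A reader might infer that this is false because 8 hospitals per arm cap the effective size at 8/0.031 = 258 patients per arm. The documents do not support that. The cap concerns adding patients at fixed 3-year rates, whereas an event-driven trial can also follow patients for longer. Following the same 473 per arm to about 50% vs 35% gives about 403 events and about 80% power (74% with 14 df) if the ICC holds. The Discussion sentence is therefore not part of this point.

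**The test may be one of equivalence.** The Analysis section names equivalence tests, and the 10% is called acceptable, which could describe a margin. That reading does not rescue the target: power is then about 28-46%.

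**Conclusion.** The point holds as an arithmetic error in the Sample size section. The 198 events do not follow from the stated design effect, which gives about 403, and 473 per group contains no allowance for clustering. At the stated ICC, power is below 80% on every two-sided reading checked: about 45-50% at 198 events for HR 0.63, and about 51-74% for 10-point gaps from 30% vs 20% down to 20% vs 10% with 473 per arm. Roughly 80% applies only to an effect near 27% vs 15%.

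These figures rest on about 59 patients per hospital, equal cluster sizes, the design effect applied to events or patients as the protocol describes, and a death-based effect. The exact shortfall moves with the control rate and the ICC. That 198 does not follow from the section's own inputs does not.

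**What to change.** Rewrite the end of the Sample size section to say that:
- 473 per group, with 87 vs 57 events, is the size for individual randomisation and is not cluster-inflated;
- with 8 hospitals per group and ICC 0.031, DE is 2.80, and 198 events give about 45-50% power for HR 0.63, shown with the range over ICC and control rate as in Step 4;
- roughly 80% power (74% with 14 df) applies only to an effect near 27% vs 15%;
- the 10% is either a superiority difference or an equivalence margin, with the power for that test.

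The cost is a rewording and a less favourable stated power. No extra patients are requested, and the Discussion sentence on event-driven design can stay.

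### The 198-event closing rule is sized on deaths, but it fires on endpoint events, and the protocol elsewhere defines the endpoint to include nonfatal cerebro-cardiovascular events

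*Protocol article*

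**What the plan says.** The Sample size section of the protocol article states: "The primary endpoint of the study is death rate, which will be determined by survival analysis". Its inputs all concern death. The reference figure from the IDEAL study is that "the death rate was 37% during a median follow-up period of 3.59 years". The planning rate is given as "we assume the death rate will be 30% or less within 3 years". The effect size is that "a difference of 10% in death rates between these two groups is considered acceptable". With "alpha = 5%, (1-beta) = 80%, patients are assigned 1:1", a log-rank calculation gives 87 versus 57 events and 473 patients per group. After allowance for clustering the total becomes 198 (128 versus 70), and the section ends: "We will complete the study when we get enough endpoint events, which is 198 events".

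Two other places define the endpoint differently. The Primary endpoint section says: "The primary endpoint will be all-cause mortality and acute nonfatal cerebro-cardiovascular events before and after dialysis initiation". The abstract (Methods) says: "The primary endpoint will be the difference of all-cause mortality and acute nonfatal cerebro-cardiovascular events between the two groups".

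The article does not limit the 198 to deaths and gives no nonfatal event rate.

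**The concern.** In an event-driven trial the closing count fixes both the length of follow-up and the information available for the primary comparison. The Discussion relies on this and says that event-based closure protects power when events are fewer than predicted. That protection works only if the counted event is the one that was powered. Here the count comes from mortality, while the word used in the rule points to an endpoint that is defined elsewhere as broader.

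Two people applying the rule in good faith could close the trial at different times and with different numbers of deaths. Closure cannot readily be undone.

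**Working it through.** **1. Does the target rest on deaths alone?** Inputs from the Sample size section: 30% deaths at 3 years, a 10-point difference (taken as 30% versus 20%), alpha 5%, power 80%, 1:1 allocation. Two-sided alpha is assumed; one-sided alpha gives 113 events and does not fit.

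- Hazards: −ln(0.7)/3 = 0.1189 and −ln(0.8)/3 = 0.0744 per year.
- Hazard ratio: 0.0744/0.1189 = 0.626 (or 1.598 inverted), with |ln HR| = 0.469.
- Schoenfeld events: 4 × (1.960 + 0.842)² / 0.469² ≈ 143. The plan has 87 + 57 = 144.
- Split by arm: with 473 per group, uniform entry over the stated 30 months and 36 months in total (the total is assumed), expected deaths are 473 × 0.1849 = 87.4 and 473 × 0.1208 = 57.1. These match 87 versus 57.

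The base of 144 is therefore a count of deaths. The plan's inflation to 198 is 198/144 = 1.375.

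**2. What remains for the death comparison if nonfatal events are counted?** The nonfatal share is an assumption. Deaths d = 198 × (1 − share). Power = Φ(√(d/1.375)/2 × 0.469 − 1.96).

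| Nonfatal share of the 198 | Deaths | d/1.375 | Power for the death difference |
|---|---|---|---|
| 0% | 198 | 144.0 | 80% |
| 10% | 178 | 129.6 | 76% |
| 20% | 158 | 115.2 | 71% |
| 30% | 139 | 100.8 | 65% |
| 40% | 119 | 86.4 | 59% |
| 50% | 99 | 72.0 | 51% |

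If first events are counted, some patients with a nonfatal event die later but before closure, so total deaths are slightly higher than in the table.

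**3. The same question by rate.** Assume 946 patients (2 × 473), uniform 30-month entry, exponential hazards, no dropout, and first nonfatal events at 2, 5 or 8 per 100 patient-years in both arms. Only the 30-month window and the 473 are in the protocol, and the protocol does not say that 473 per group belongs with the clustered 198.

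- 198 deaths are reached at about 3.7 years from first entry.
- 198 first composite events are reached at about 3.3, 2.9 or 2.6 years, with about 167, 136 or 116 deaths in all.
- Power for death on the 1.375 scale is then about 74%, 65% or 58%.

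If patients are scaled with events instead (473 × 198/144 ≈ 650 per group), the dates become 3.0 years for deaths and 2.7, 2.4 or 2.2 years for the composite. The death counts barely move. The dates therefore depend on the assumed number of patients, while the loss of deaths hardly does.

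**4. Does 198 serve the composite?** If the composite hazard ratio is also 1.598, 198 events keep the planned 80%. If nonfatal rates are equal in the two arms, the composite hazard ratios at the three assumed rates are (0.1189 + λ)/(0.0744 + λ) = 1.47, 1.36 and 1.29. Before any clustering, 198 events then give 78%, 58% and 43% power. The plan does not state a composite hazard ratio.

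**The case against.** The strongest reply is that the Sample size section answers the question itself. It opens by calling the primary endpoint death rate, so endpoint events in its last sentence most naturally means deaths, and nothing then closes early. That reading is fair, and it is why a reader should not infer that early closure is certain or planned. It does not remove the conflict, because the abstract and the Primary endpoint section name the broader endpoint and the closing rule does not say which definition it uses.

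A second reply is that the size of the loss rests on rates the protocol does not give. This also stands. With a 10% nonfatal share the cost is about 20 deaths and 4 points of power, and only the larger shares do serious damage. If treatment acts on nonfatal events as it does on death, the composite comparison loses nothing.

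Three stronger inferences are tempting but not supported.

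- One is that the plan implies a 36-month minimum duration, so that closure before then would breach it. The 87 versus 57 split also arises from other accrual and total times, for example 2 and 2.74 years or 3 and 3.26 years. The 36 months is only one consistent value.
- Another is that early closure would end the study before late entrants reach the eGFR at which the arms differ. The article gives no rate of eGFR decline, so this cannot be shown.
- The third is that a patient with a nonfatal event who later dies will be counted twice. Counting rules may stand in the full protocol or the analysis plan, which are not shown.

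**Conclusion.** The concern holds as an unresolved conflict over what the closing count counts. The 198 derives from mortality assumptions only, as the reproduction of 144 confirms, while two other places in the article define the endpoint to include nonfatal events. On the composite reading, and assuming that 10% to 50% of counted events are nonfatal, 178 to 99 deaths remain. Power for the planned death difference is then 76% to 51% instead of 80%. These figures assume a hazard ratio of 0.626, two-sided 5% alpha and the plan's own inflation of 1.375.

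A reader might take from this that 198 deaths would secure 80% power. The documents do not support that either. With 473/8 = 59.1 patients per cluster and an ICC of 0.031, the plan's own formula gives a design effect of 1 + 58.1 × 0.031 = 2.80. Then 144 × 2.80 ≈ 403 events would be needed, and 198 deaths give only about 50% power (198/2.80 ≈ 71 effective events). That is a separate defect. It bears on how the fix is worded but not on whether this point holds.

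**What to change.** Name one primary endpoint, in the same terms, in the abstract, the Primary endpoint section and the Sample size section. Then state in the Sample size section which events trigger closure, in one of two ways:

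- If death is primary, closure is triggered by deaths from any cause only, and nonfatal events do not count towards it.
- If the composite is primary, re-derive the count from composite event rates and a stated composite hazard ratio, and count each patient once, at the first event.

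In both cases restate the power that the count delivers under the stated ICC, number of clusters and design effect. The text should not suggest that 198 secures 80%.

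The death-only option costs wording and a change to event tracking. If composite events have been counted so far, follow-up will be longer. The composite option may cost more. At the illustrative hazard ratios of 1.36 and 1.29, about 335 and 490 events are needed for 80% power before any clustering, well above 198. That would mean longer follow-up or more patients.
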